#### Identification of potential biomarkers

Confirmation of potential biomarkers involves determining their retention time in the original chromatogram, as well as utilizing accurate molecular weight, isotope distribution, and ion information (parent ions, fragment ions, adduct ions, and multiply charged ions) provided by TOFMS. This information, along with assistance from the PeakView™ software, aids in calculating the possible molecular formula. Preliminary identification of potential biomarkers is conducted by searching databases such as ChemSpide, MassBank, MetFrag, and Metlin. Finally, the identification is confirmed by using corresponding reference standards.

#### Metabolic pathway analysis

Through the analysis of the correlation between the levels of potential biomarkers and the scores of related scales, we identified relevant biomarkers in acupuncture treatment for children with TD. Additionally, we examined the KEGG database to identify metabolic pathways associated with these biomarkers in acupuncture treatment for TD children. Drawing upon this information, we constructed physiological and biochemical metabolic pathways in vivo related to the biomarkers, thus providing insights into the mechanism of acupuncture treatment for TD children.

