**Methods:**

This randomized controlled trial will recruit a total of 90 children, in which they will be divided into non-intervention group and intervention group. The non-intervention group consists of 30 healthy children while the intervention group consists of 60 children with tic disorder. The intervention group will be randomly allocated into either the treatment group or the control group, with 30 children randomly assigned in each group. Children either received acupuncture treatment and behavioral therapy (treatment group) or sham acupuncture treatment and behavioral therapy (control group), 3 treatment sessions per week for a period of 12 weeks, with a total of 36 treatment sessions. Outcome measures include YGTSS, urinary and fecal metabolomics, infrared thermography of body surface including governor vessel. For the intervention group, these outcome measures will be collected at the baseline and 90th day prior to intervention. Whereas for the non-intervention group, outcome measures (excluding YGTSS) will be collected at the baseline.

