**Discussion:**

The main outcome will be to observe the changes of the severity of tic condition, the secondary outcome will be to observe the changes of structural characteristic of infrared thermography of body surface/acupoints along the governor vessel and to evaluate the changes of urinary and fecal metabolomics at the end of the treatment, so as to analyze the relationship between them and to provide further knowledge in understanding the possible mechanism of acupuncture in improving the clinical symptoms via regulating and restoring the body metabolomics network, which in future it can develop as a set of clinical guideline (diagnosis, treatment, assessment, prognosis) in treating tic disorder. ChiCTR2300075188(Chinese Clinical Trial Registry, http://www.chictr.org.cn, registered on 29 August 2023).

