#### Multivariate Statistical Analysis

Preprocessed data will be subjected to unsupervised data analysis using Principal Component Analysis (PCA). A score plot will be used to observe clustering of data from different groups and to remove outlier samples. A loading plot will be utilized to identify components that contribute to inter-group variability, with special attention given to excluding prototype compounds and their metabolites. Additionally, univariate analysis such as fold change (FC) and t-tests will be performed to identify components that exhibit significant statistical differences. Pattern recognition methods, such as Partial Least Squares Discriminant Analysis (PLS-DA) and Orthogonal Partial Least Squares Discriminant Analysis (OPLS-DA), will be employed, and targeted programming and execution using languages such as R or C will be based on the characteristics of the analysis data. Integration of HILIC-TOFMS and RPLC-TOFMS data will be conducted to identify differential components. Multiple methods, including t-tests (*p* < 0.05), FC analysis (FC > 2), and PLS-DA (VIP > 1.5), will be used to screen and confirm potential biomarkers that contribute to inter-group differences, thus identifying potential biomarkers associated with acupuncture treatment in children with TD.

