### Other indicators

Observations and recordings will be made during the initial visit on the first day and during the follow-up visit at the 12th week.

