## Statistical analysis

Descriptive statistical analysis, qualitative indicators are described by frequency table, percentage or composition ratio; Quantitative indicators are described by mean, standard deviation, or median, lower quartile (Q1), upper quartile (Q3), minimum value and maximum value.

The qualitative data are analyzed using the chi-square test, Fisher’s exact probability method, Wilcoxon rank sum test, CMH χ2 test, and WLS covariance. For the quantitative data, the normal distribution is verified using the t test (homogeneity test of variance is conducted between groups, with a test level of 0.05, and the Satterthwaite method is used for correction when the variance is uneven). For non-normal distribution, the Wilcoxon rank sum test and Wilcoxon signed rank sum test are employed, along with GLM covariance. A two-sided test is uniformly used for the hypothesis testing, and test statistics along with their corresponding P-values are provided, with *P* ≤ 0.05 indicating statistical significance and *P* ≤ 0.01 indicating high statistical significance.

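### Naming acupuncture-related biomarkers by correlating metabolite levels with scale scores can reflect arm or visit, not a link in the individual child, if groups are pooled

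*Protocol article*

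**What the plan says.** Two sections of the protocol article describe the route from metabolite to biomarker.

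- **Multivariate Statistical Analysis.** Metabolites are chosen by t-test (p < 0.05), fold change (> 2) and PLS-DA (VIP > 1.5). These criteria "will be used to screen and confirm potential biomarkers that contribute to inter-group differences".
- **Metabolic pathway analysis.** The chosen metabolites are taken forward through "the correlation between the levels of potential biomarkers and the scores of related scales". The conclusion attached to this step is that "we identified relevant biomarkers in acupuncture treatment for children with TD". KEGG pathways and an account of mechanism follow from it.

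The Discussion part of the abstract makes the link between symptoms, thermography and metabolomics an aim of the trial: the outcomes are observed "so as to analyze the relationship between them".

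On who and when, the Methods part of the abstract says "Whereas for the non-intervention group, outcome measures (excluding YGTSS) will be collected at the baseline". Only children with tic disorder therefore have a YGTSS score. Under Other indicators, "Observations and recordings will be made during the initial visit on the first day and during the follow-up visit at the 12th week". Table 1 schedules both YGTSS and metabolomics at baseline and at week 12.

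The correlation is stated in terms of levels. The article does not say which arms or visits enter it, nor that arm or visit is adjusted for.

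**The concern.** The trial's hypothesis is that acupuncture lowers the YGTSS and also changes the metabolite profile. If both happen, a treated child tends to have a lower score and a shifted metabolite simply by being in the treated arm. Putting both arms into one correlation then yields a non-zero coefficient even when, among children in the same arm, the metabolite says nothing about the score. Pooling baseline and week 12 does the same if both variables drift over time.

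Selecting metabolites for inter-group difference favours those that can behave in this way. A positive result therefore could not separate the proposed mechanism (the metabolite carries the symptom effect) from two parallel effects of treatment. The pathway and mechanism conclusions rest on this step.

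**Working it through.** **Inputs from the article.** Planned size is 30 per arm with 20% dropout allowed (Sample size), so 30 × 0.8 = 24 completers per arm. Tests are two-sided at 0.05 (Statistical analysis). Visits are baseline and week 12. The t-test screen is at p < 0.05.

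**Assumptions.** The article gives no SD for the YGTSS or any metabolite, so shifts of 0.5, 0.8 and 1.2 SD are tried. Within each arm the true correlation between metabolite and score is set to zero.

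**The plan's own figure.** None is given for the correlation step. The only derived figure is 30 per arm, from response rates of 95% and 55%. Power is not stated. At 90% power, two-sided, without continuity correction, 23 per arm are needed, and 23 / 0.8 = 28.75, or 29. At 80% power with continuity correction the need is 22, and 22 / 0.8 = 27.5, or 28. So 30 is reproduced to within 2 per arm, and 24 and 30 are used below.

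**Correlation created by arm alone.** Let G be the arm indicator (0 or 1, equal arms, variance 1/4), metabolite = mG + noise and score = −dG + independent noise, each with noise SD 1. The covariance is −md/4 and the variances are 1 + m²/4 and 1 + d²/4, so

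|r| = (md/4) / √[(1 + m²/4)(1 + d²/4)].

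- m = d = 0.5: 0.0625 / 1.0625 = 0.06
- m = d = 0.8: 0.16 / 1.16 = 0.14
- m = d = 1: 0.25 / 1.25 = 0.20
- m = d = 1.2: 0.36 / 1.36 = 0.26

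**How often it is declared significant.** There were 3,000 simulated trials per setting. A metabolite was kept only if its between-arm t-test had p < 0.05 (the fold-change and VIP screens were not simulated). The pooled week-12 Pearson test was then compared with the same test after centring each variable within arm. Rates are among kept metabolites.

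| Shift in both (SD) | Per arm | Kept | Pooled, p < 0.05 | Within arm, p < 0.05 |
|---|---|---|---|---|
| 0.5 | 24 | 39.2% | 9.4% | 3.9% |
| 0.8 | 24 | 77.0% | 17.8% | 4.7% |
| 1.2 | 24 | 97.8% | 46.5% | 5.4% |
| 0.5 | 30 | 47.5% | 9.3% | 4.7% |
| 0.8 | 30 | 86.0% | 20.8% | 5.4% |
| 1.2 | 30 | 99.7% | 55.7% | 5.4% |

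**When nothing goes wrong.** With no score difference between arms (d = 0) and metabolite shifts of 0.5 to 1.2 SD, the pooled rate is 4.3% to 5.5%. Selection by itself does not inflate the error; the score must differ too.

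**Visits pooled.** With 48 children (2 × 24), an assumed correlation of 0.5 between a child's two values of the same variable, and both variables shifting over time, the pooled rates are 12.1%, 29.0% and 78.2% for shifts of 0.5, 0.8 and 1.2 SD. Correlating change with change instead gives 5.2%, 5.2% and 4.9%.

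**The case against.** The strongest reply is that no section says arms or visits are pooled. The selection section speaks only of groups, and the Metabolomics outcome section describes sampling of healthy children and children with tic disorder. Metabolites could therefore be chosen for a healthy-versus-tic difference and correlated with the YGTSS at baseline. Healthy children have no YGTSS, so that route cannot create the artefact; nor can a correlation inside one arm at one visit. A condensed article may also leave population, visit and covariates to a fuller document. This stands, and it makes the point conditional. It does not remove it: what the article does state is levels against scores, read as biomarkers of acupuncture treatment and as insight into mechanism, with no restriction that would rule pooling out.

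A reader might infer three stronger things that the documents do not support.

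- **That selection on group difference itself produces the correlation.** It does not unless the score also differs between the pooled groups.
- **That every metabolite differing by arm will be linked to symptoms.** At 0.8 SD and 24 per arm the induced correlation is 0.14, and about 82% of such metabolites (100 − 17.8) would not reach significance.
- **That the plan treats two visits as independent observations.** Doing so with 60 values per visit and 1 SD shifts would give about 60% false positives, but no section proposes it.

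It is also fair that the article already speaks of potential biomarkers and lists its small sample as a limitation, and that the randomised comparison on the YGTSS is untouched. Adjusting for arm would still yield an association, not proof of mechanism.

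**Conclusion.** The point holds in conditional form. The stated method, levels correlated with scores after a screen for group difference, cannot tell a child-level link from two parallel treatment effects if the arms (or the visits) are pooled, and the article neither states nor excludes pooling.

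For pooled arms at week 12, a test at 5% rejects in roughly 9% to 47% of cases with 24 per arm and 9% to 56% with 30 per arm. These ranges rest on assumed equal shifts of 0.5 to 1.2 SD in both variables and no true within-arm correlation. At the low end the effect is modest; at the high end about half of such metabolites would be falsely linked to symptoms. It should be corrected because the mechanism conclusion depends on this step. It does not affect the primary outcome.

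**What to change.** In Metabolic pathway analysis, replace the correlation of levels with a linear model fitted among the randomised children with tic disorder:

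YGTSS change (week 12 minus baseline) = intercept + β × metabolite change + arm + baseline YGTSS + baseline metabolite.

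Report β with its confidence interval for each metabolite, and describe the results as exploratory association, not as evidence of mechanism. The arm term is needed even with change scores, because treatment can shift both changes. This exact model was not simulated; it combines the two devices that were (removing arm, and using change), each of which brought the error back close to 5%.

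The cost is a few sentences. Table 1 already schedules both measurements at both visits, and recruitment was still open at the article's Trial status statement. The downside is that fewer metabolites will be reported as linked to symptoms, and children without week-12 data drop out of this analysis.

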## Observation time point

### Main symptoms and signs

Observations and recordings will be made during the initial visit on the first day and during the follow-up visit at the 12th week.

### Other indicators

Observations and recordings will be made during the initial visit on the first day and during the follow-up visit at the 12th week.

## Adverse events

Various adverse reactions that may occur during acupuncture treatment include dizziness, bleeding, infection, low fever, and organ damage. Infrared thermal imaging is a harmless and non-invasive method that poses no radiation risk to children. However, it requires exposing the back area during imaging, which may increase the risk of children catching a cold. The collection of feces may frighten children, leading to crying. Allergic reactions may occur in the control group when the acupuncture needle comes into contact with the skin during sham acupuncture. Additionally, sham acupuncture may cause pain, causing children to cry out of fear and discomfort. All adverse reactions observed during the study will be truthfully recorded.

## Quality control

The YGTSS scale will be assessed by a qualified physician. Standard operating procedures and quality control procedures will be established for observing indicators using infrared thermal imaging, with computer-generated results and traceable data and images. We will analyze and process the data through professional instruments to ensure the accuracy of the data. Prior to the project commencement, researchers received training on the experimental protocol, and the consistency of quantitative symptom and sign assessment standards was tested. Researchers signed a statement of commitment. Researchers should diligently obtain informed consent to ensure that participants fully understand the experimental requirements and are willing to cooperate. Treatment compliance of patients in the experimental group is monitored using the treatment count method. Compliance is calculated as the actual number of treatments received divided by the initially scheduled number of treatments, multiplied by 100%. Compliance rates below 80% or above 120% are considered major violations of the experimental protocol. The results before and after treatment should be communicated to the families of the patients.

## Data management and monitoring

The researchers will use research medical records to collect data and establish a database. The recorded data in the research medical records will be summarized and analyzed to generate the final conclusions and research report. Upon completion of the study, the database will be locked for security purposes. The personal information of the participants will be treated as confidential. Documents related to quality control, such as original records of data consistency check, numerical range and logic check, and blind audit, will be preserved. Meanwhile, we have trained researchers to establish a good communication relationship with patients. For patients who discontinue or deviate from intervention protocols, we will try to get as much trial data as possible by telephone, if the patient is willing to provide it. In addition, a safety monitoring committee will be established to review and interpret the data of trial. They will review the progress of the trial, independently of the investigators, and decide whether the trial needs to be terminated early solely on the basis of adverse events.

## Statistical analysis

Descriptive statistical analysis, qualitative indicators are described by frequency table, percentage or composition ratio; Quantitative indicators are described by mean, standard deviation, or median, lower quartile (Q1), upper quartile (Q3), minimum value and maximum value.

The qualitative data are analyzed using the chi-square test, Fisher’s exact probability method, Wilcoxon rank sum test, CMH χ2 test, and WLS covariance. For the quantitative data, the normal distribution is verified using the t test (homogeneity test of variance is conducted between groups, with a test level of 0.05, and the Satterthwaite method is used for correction when the variance is uneven). For non-normal distribution, the Wilcoxon rank sum test and Wilcoxon signed rank sum test are employed, along with GLM covariance. A two-sided test is uniformly used for the hypothesis testing, and test statistics along with their corresponding P-values are provided, with *P* ≤ 0.05 indicating statistical significance and *P* ≤ 0.01 indicating high statistical significance.

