**Fig. 3 Fig3:**
[figure not shown]
Infrared thermographic changes in the back of TD patients. The thermal distribution on the back before and after acupuncture treatment in individuals with TD is presented from left to right

Therefore, we designed this randomized controlled trial to compare the changes of the severity of tic condition before and after the intervention, and to observe the changes of structural characteristic of infrared thermography of body surface/acupoints along the governor vessel and to evaluate the changes of urinary and fecal metabolomics at the end of the treatment. By comparing both the non-intervention group and intervention group, we hope to analyze the relationship between them and to provide further knowledge in understanding the possible mechanism of acupuncture in improving the clinical symptoms of TD via regulating and restoring the body metabolomics network.

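### The stated rule for quantitative outcomes misuses the t test as a normality check, lets the data pick the test, and gives YGTSS no stated baseline adjustment when data are normal

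*Protocol article*

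**What the plan says.** The Statistical analysis section gives one general rule for all quantitative outcomes and does not mention YGTSS by name. It has two branches.

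- **Normal data.** "For the quantitative data, the normal distribution is verified using the t test". A parenthesis adds a between-group test of equal variances at the 0.05 level, after which "the Satterthwaite method is used for correction when the variance is uneven". No covariance model appears in this branch.
- **Non-normal data.** "For non-normal distribution, the Wilcoxon rank sum test and Wilcoxon signed rank sum test are employed, along with GLM covariance". The GLM covariance analysis has no named outcome and no named covariate.

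A covariance method is also listed for qualitative data ("Wilcoxon rank sum test, CMH χ2 test, and WLS covariance"), again without a covariate.

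YGTSS is the primary outcome. Table 1 schedules it at baseline and week 12, and the Observation time point section agrees: "Observations and recordings will be made during the initial visit on the first day and during the follow-up visit at the 12th week". The abstract words the aim as change: "The main outcome will be to observe the changes of the severity of tic condition". The end of the Introduction says the trial will "compare the changes of the severity of tic condition before and after the intervention". The later section on thermographic images has its own test rules, which apply to skin temperature only.

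**The concern.** Three features of the rule are badly fixed.

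1. As printed, the t test is assigned a job it cannot do. It compares means and says nothing about distributional shape. No actual normality check is named.
2. The test applied to the primary outcome is decided after the data are seen. Normality selects the t or rank branch, and a variance pre-test then selects the t-test variant.
3. Covariance adjustment is tied to the non-normal branch, where the usual assumptions of a linear covariance model fit least. It is absent from the normal branch, where they fit best.

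At stake is precision in a small trial. The Sample size section has 30 children per arm and 20% dropout, so about 24 per arm may be evaluable. The article's closing discussion itself names small size and possible high dropout as limitations. Baseline YGTSS is already being collected, so using it efficiently costs nothing. A reader also cannot tell which single result will stand as the primary comparison of acupuncture with sham.

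**Working it through.** **The plan's own figure.** The Sample size section gives effectiveness rates of 95% and 55%, 20% dropout, and 30 per arm. Power is not stated. With two-sided 5% and an assumed 90% power, the pooled two-proportion formula uses a mean rate of 0.75:

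n = [1.96·√(2·0.75·0.25) + 1.28·√(0.95·0.05 + 0.55·0.45)]² / 0.40² ≈ 22.5, so 23 per arm.

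23 / 0.8 = 28.75, so 29 per arm, or 58 in total. This is within two of the stated 60. The sample size is therefore not at issue here, but it rests on a response rate and gives no YGTSS standard deviation or target difference.

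**Inputs for the YGTSS comparison**

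- From the article: 30 per arm less 20% leaves 24 per arm; two-sided test; 5% level.
- Assumed, because the article gives none: true difference 0.6 SD, equal SD at baseline and week 12, and baseline-to-week-12 correlation r of 0.3, 0.5 or 0.7.

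**Variance relative to week-12 scores alone**

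- Change score: 2(1 − r), which gives 1.40, 1.00 and 0.60.
- ANCOVA: 1 − r², which gives 0.91, 0.75 and 0.51.
- ANCOVA relative to change score: (1 − r²) / [2(1 − r)] = (1 + r)/2, which gives 0.65, 0.75 and 0.85.

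**Power.** This comes from the noncentral t distribution, with noncentrality 0.6·√(24/2) / √(variance factor). For week-12 scores alone the noncentrality is 0.6 × 3.464 = 2.08 on 46 degrees of freedom.

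| Analysis | r = 0.3 | r = 0.5 | r = 0.7 |
|---|---|---|---|
| t test on week-12 scores | 53% | 53% | 53% |
| t test on change scores | 41% | 53% | 75% |
| ANCOVA | 57% | 65% | 81% |

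Using 45 degrees of freedom for ANCOVA, to allow for the covariate, leaves these rounded figures unchanged.

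**Detectable difference at 80% power.** This is 0.83 SD for week-12 scores. For ANCOVA it is 0.83·√0.75 = 0.72 SD at r = 0.5 and 0.83·√0.51 = 0.59 SD at r = 0.7.

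**Cost of the pre-test rule.** Null data were simulated with 24 per arm and 8,000 runs, assuming Shapiro-Wilk as the normality check and a variance test choosing the t-test variant. The rule rejected in about 5.2% of runs for both normal and lognormal data. Reporting whichever of the t and rank-sum p-values was smaller gave 6.0% (normal) and 6.7% (lognormal).

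**The case against.** The strongest reply is that the section is a general menu in a condensed article, and that a separate analysis plan may name the final model. The t-test sentence is most likely a slip: the thermography section states the logic correctly, and the parenthesis about variances only makes sense if the t test is the analysis. This stands as an explanation. It does not make the printed sentence right, and an analysis plan that specified ANCOVA for normal data would differ from the rule printed here.

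A reader might infer several stronger things that the article does not support.

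- **That baseline YGTSS is discarded.** The article does not say so. The aim is worded as change, a change score or signed-rank test uses the baseline value, and GLM covariance is on the list and could carry it.
- **That ANCOVA is worth raising 48 evaluable children to 64 or 94.** Those figures are 48/0.75 and 48/0.51. They compare only with a week-12-only test, which the article never specifies. Against change scores at r = 0.7 the equivalent is 48/0.85, about 56, and the power gap is 75% against 81%. At r = 0.8 the variance ratio is 0.90 and the gain nearly vanishes.
- **That the pre-test inflates false positives.** The simulated rate of about 5.2% does not bear this out.
- **That the primary test will be within-arm.** The before-and-after wording and the signed-rank test permit that reading. But the variance test is between groups, the rank-sum test is listed, and the Introduction presents the trial as a randomised comparison.

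**Conclusion.** The point holds in a limited form. The normality sentence is wrong as printed. The stated rule leaves the choice of test for YGTSS to the data. Its normal-data branch carries no stated baseline adjustment, while the only covariance model for quantitative data sits in the other branch without an outcome or covariate.

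The loss is one of precision and of a fixed primary result, not of type I error control. Against a change-score t test, ANCOVA gains about 16, 12 and 6 percentage points of power at r = 0.3, 0.5 and 0.7. Against week-12 scores alone the gains are about 4, 12 and 28 points. All of these rest on the assumed 0.6 SD difference, 24 per arm and the assumed correlations. The direction does not: under equal SDs at the two visits, the ratio (1 + r)/2 is below 1 for every r below 1. This is an improvement that should be made, not a flaw that invalidates the trial.

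**What to change.** Replace the normality sentence, and state one primary between-arm analysis for YGTSS: a linear model of week-12 YGTSS total on randomised arm, with baseline YGTSS total as covariate, tested two-sided at 5% and reported as the adjusted difference with its 95% confidence interval. Say that it is fitted whatever a normality or variance pre-test shows. Keep a rank-based analysis as sensitivity, and label within-arm before-and-after tests as descriptive.

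The cost is wording only, since both YGTSS measurements are already scheduled. The article says recruitment is still under way, so the change can be made and dated before the data are unblinded.
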